### Blinding

The therapist responsible for administering the intervention could not be blinded to treatment allocation because knowledge of the device setting was necessary to deliver either active photobiomodulation or sham photobiomodulation according to the study protocol. To minimize potential performance bias, the therapist followed a standardized intervention protocol, with identical patient positioning, application procedures, treatment duration, and interaction with participants in both groups. The sham intervention reproduced the same procedures as the active intervention, except for the absence of therapeutic light emission.

The therapist was not involved in outcome assessment or data analysis. Participants were blinded to treatment allocation through the use of fully occlusive protective goggles, which prevented the perception of light emission. Neither the active nor sham intervention produced a sensation of heat. Outcome assessors and data analysts also remained blinded to group allocation. At the end of the intervention, participants were asked to indicate which treatment they believed they had received, allowing assessment of the success of participant blinding by comparing their perceived allocation with their actual treatment allocation.

Unblinding occurred only in the event of a serious adverse event or when knowledge of treatment allocation was required for clinical decision-making and was performed by an independent researcher who was not involved in outcome assessment or data analysis.

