Urinary incontinence	International Consultation on Incontinence Questionnaire–Short Form (ICIQ-SF)	Assesses the frequency and amount of urinary leakage and its impact on quality of life.	Total score ranging from 0 to 21.	T3 and T4	Reduction of approximately 2.5–5 points; changes of ≥ 4 points represent a clinically important improvement.
Sexual function	Female Sexual Function Index (FSFI)	Assesses sexual desire, arousal, lubrication, orgasm, satisfaction, and pain during the previous four weeks.	Total score ranging from 2 to 36; cutoff score = 26.55.	T4	Score > 26.55, indicating preserved sexual function.
Adverse events	Standardized clinical record	Assessment of intervention-related adverse events (increased pain, discomfort, skin irritation, hematoma, allergic reaction, or other complications).	Presence/absence; classified according to type and severity.	T1, T2, T3, and T4	Absence of serious treatment-related adverse events.

Legend *T0* pre-intervention, *T1* immediately after the intervention, *T2* 12 hours after the intervention, *T3* 40 days postpartum (late postpartum period), *T4* 3 months postpartum (remote postpartum period)

The baseline assessment will include the collection of sociodemographic and obstetric data, followed by a standardized physical examination. Perineal pain intensity will be assessed using the Numeric Rating Scale (NRS) and pressure algometry. The NRS is an 11-point scale ranging from 0 (no pain) to 10 (the worst pain imaginable), with pain categorized as mild (1–3), moderate (4–6), or severe (7–10). Pain intensity will be assessed using standardized verbal descriptors [18]. 

Pressure pain threshold will be measured using a calibrated MED.DOR^®^ digital pressure algometer, with readings expressed in kgf/cm². The device will be applied perpendicularly to the bilateral peritraumatic region, with one measurement obtained on each side. Participants will be instructed to indicate the moment when the sensation of pressure becomes painful by saying “stop,” and this value will be recorded as the pressure pain threshold. To ensure biosafety, the algometer probe will be covered with disposable plastic film and disinfected with 70% alcohol before each assessment [19].

The use of analgesic medication will be recorded at each assessment point, including the type of medication, dose, route of administration, and time elapsed between medication administration and pain assessment.

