All study outcomes will be assessed by previously trained examiners who will remain blinded to participant allocation. The assessment instruments used in this study (NRS, pressure algometry, VAS for satisfaction, Global Perceived Effect Scale, WHODAS 2.0, ICIQ-SF, and FSFI) have demonstrated adequate psychometric properties, including validity and reliability, and are widely used in clinical research involving women during pregnancy and the postpartum period. 

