### Patient safety

Participant autonomy will be fully respected, and participants may withdraw from the study at any time without any consequences. Discontinuation criteria include refusal to continue the assessments or the intervention.

Potential risks include mild discomfort during the assessments, transient pain during pressure algometry, and a minimal risk of infection. These risks will be minimized through standardized procedures, private assessment settings, and rigorous equipment disinfection protocols.

In the event of an adverse event, the intervention will be discontinued immediately. All participants will have access to comprehensive medical care at University Hospital, including legally required compensation, if applicable.

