### Adverse events

Adverse events related to photobiomodulation are expected to be minimal. Any discomfort, increase in pain, or unexpected reaction occurring during or after treatment will be recorded and monitored. Participants will be actively questioned about adverse events at each assessment. If any risk or complication arises, the intervention will be discontinued immediately, and appropriate clinical care will be provided.

Participants who withdraw because of adverse events will remain included in the analyses according to the intention-to-treat principle.

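### Table 3 limits the adverse-event outcome to intervention-related events while other sections record and follow any event, so the PBM-versus-sham harm result depends on which text is applied

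*Protocol article*

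**What the plan says.** The adverse-event row of Table 3 (Participant characteristics and outcome assessments) describes the outcome as "Assessment of intervention-related adverse events (increased pain, discomfort, skin irritation, hematoma, allergic reaction, or other complications", assessed at T1 to T4. The scoring column reads "Presence/absence; classified according to type and severity". The column for a clinically meaningful effect reads "Absence of serious treatment-related adverse events". The restriction to related events thus appears twice, in the outcome and in the criterion. Relatedness is not among the attributes to be scored, so it acts as a condition of entry to the outcome.

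The Adverse events section is wider: "Any discomfort, increase in pain, or unexpected reaction occurring during or after treatment will be recorded and monitored". It adds: "Participants will be actively questioned about adverse events at each assessment". Neither sentence asks whether the event was caused by the intervention. The Post-trial care section says that any adverse event identified in the trial is followed to resolution, again without a causality condition.

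On who collects the data, the text below Table 3 says: "All study outcomes will be assessed by previously trained examiners who will remain blinded to participant allocation". The Blinding section says of the therapist, who knows the arm: "The therapist was not involved in outcome assessment or data analysis".

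**The concern.** A sham arm is useful for safety because it shows how often events occur without the active light. Comparing all events by arm estimates the excess due to PBM without anyone having to judge the cause of a single event. An outcome that admits only intervention-related events puts that individual judgement back in front of the comparison.

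The judgement is especially hard here. Inclusion requires pain of at least 3 on the NRS and first- or second-degree trauma and/or vulvar edema, within 12 h of birth. Three of the event types that Table 3 lists (increased pain, discomfort, hematoma) can arise from the birth injury itself. An examiner who does not know the arm cannot separate them from an effect of light that half the women did not receive.

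At stake is the safety conclusion. The abstract promises evidence on efficacy and safety, and the Conclusion makes future use conditional on both. Two analysts, one following Table 3 and the other the Adverse events section, could report different harm results from the same records.

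**Working it through.** The plan states no figure for this outcome, so there is none to reproduce. The check is mainly a comparison of texts, followed by an illustration of size.

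**1. The texts side by side**

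| Place | Events covered | Causality condition |
|---|---|---|
| Table 3, outcome description | Listed types plus an open last category | Yes, intervention-related |
| Table 3, criterion | Serious events | Yes, treatment-related |
| Adverse events section, recording | Discomfort, rise in pain, unexpected reaction | None |
| Adverse events section, questioning | Adverse events at each assessment | None |
| Post-trial care | Any adverse event identified | None |

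Data collection is broad and the outcome definition is narrow. Events can be asked about, recorded and followed, yet fail to enter the outcome that Table 3 says will be reported.

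**2. Whether the condition can be applied**

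Vulvar hematoma at entry is an exclusion criterion, so a vulvar hematoma seen at T1 or later can be recognised as new without judging its cause. The same holds for pain or discomfort worse than at T0. Whether the event is new or worse can be observed; whether the light caused it cannot be observed by a blinded examiner.

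**3. Illustration of size**

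Input from the documents: n = 34 per group (Sample size calculation). Assumptions, not in the documents: all-cause event risk of 20% with PBM and 10% with sham; a share q of events called related, equal in both arms because examiners are blinded; two-sided 5% test.

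With p1 = 0.20q, p2 = 0.10q and p̄ = (p1 + p2)/2,

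power = Φ{ [ |p1 − p2| − 1.96·√(2p̄(1 − p̄)/n) ] / √([p1(1 − p1) + p2(1 − p2)]/n) }.

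For q = 1: √(2 × 0.15 × 0.85/34) = 0.0866 and √((0.16 + 0.09)/34) = 0.0857, so (0.10 − 1.96 × 0.0866)/0.0857 ≈ −0.81, and Φ gives 0.21.

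| q | Expected events, PBM v sham | Risk difference | Approximate power |
|---|---|---|---|
| 1 | 6.8 v 3.4 | 10 points | 21% |
| 0.75 | 5.1 v 2.6 | 7.5 points | 16% |
| 0.50 | 3.4 v 1.7 | 5 points | 12% |
| 0.25 | 1.7 v 0.9 | 2.5 points | 8% |

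The normal approximation is rough at counts this small. The direction is what matters: an equal filter leaves the risk ratio at 2.0 but shrinks the absolute difference and thins a comparison that is weak to begin with.

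**The case against.** The best case for the plan is that the narrow wording sits in one table row, while collection is already broad: women are actively asked about events at each assessment, examiners are blinded, and events are followed to resolution. How relatedness is graded, and by whom, may stand in a fuller protocol or analysis plan that is not shown. This stands in part. The missing grading procedure is not held against the article. But Table 3 is a stated outcome definition, and it disagrees with other sections of the same article.

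It can also be argued that an accurate relatedness filter sharpens the signal by removing background events. Under the rates assumed above, a perfect filter would turn 20% v 10% into 10% v 0%. That requires knowing which events the light caused, which a blinded examiner does not.

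Furthermore, increased pain up to 12 h is captured with no filter at all, because NRS and algometry are taken in every woman at T0, T1 and T2. This stands. It confines the loss to the other event types and to pain reported at T3 and T4.

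A reader might infer more than the documents support:

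- *That named risks are missed.* The Patient safety section says: "Potential risks include mild discomfort during the assessments, transient pain during pressure algometry, and a minimal risk of infection". Pain and discomfort are listed types in Table 3, and the list ends in an open category that can take infection. Infection is not itemised, but it is not excluded.
- *That attribution would favour one arm and create or hide a difference.* This needs a judge who knows or guesses the arm. Outcome assessors are blinded and the therapist is kept out of outcome assessment. The article does not name who judges relatedness, and it permits unblinding for a serious adverse event, so the possibility is not closed, but nothing shows it to be likely.
- *That Table 1 collects events before treatment, because it marks adverse events in the T0 column.* The table is visibly broken as read, and the same column carries the mark for the G1 intervention, so the entry may cover the session itself. Nothing should rest on it.

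**Conclusion.** The point holds as an inconsistency in a stated outcome, together with a poor choice of definition. Table 3 admits only related events to the harm outcome and to the safety criterion, whereas the Adverse events and Post-trial care sections carry no such condition. In this population, blinded attribution of common local symptoms has little basis, so the expected consequence is lost events and a safety result that varies with the text followed. A bias of known direction is not shown.

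The size cannot be fixed from the documents. Under the assumed 20% v 10%, and a related share of 25% to 75%, between a quarter and three quarters of events would leave the comparison, and approximate power would be 8% to 16% in place of 21%. Even with all events counted, 34 per arm gives a weak harm comparison, which is a reason not to discard any. The pain outcome and its analysis are unaffected.

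**What to change.** Reconcile Table 3 with the Adverse events and Post-trial care sections. Define the Table 3 outcome as all adverse events that are new or worse than at baseline, regardless of cause, collected by the blinded examiners at T1 to T4 and compared by arm. State the safety criterion on the same basis. Record relatedness as a separate descriptor that does not decide whether an event is counted, and report related events as a secondary listing. Naming infection in the list is an optional clarification, since the open category already admits it.

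The cost is a revised table entry and one extra field on the case report form. The active questioning and blinded examiners needed are already planned. The downside is more events to record and list, most of them minor and many due to the birth injury; the sham arm provides the reference for reading them. No treatment or stopping rule changes.

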### Patient safety

Participant autonomy will be fully respected, and participants may withdraw from the study at any time without any consequences. Discontinuation criteria include refusal to continue the assessments or the intervention.

Potential risks include mild discomfort during the assessments, transient pain during pressure algometry, and a minimal risk of infection. These risks will be minimized through standardized procedures, private assessment settings, and rigorous equipment disinfection protocols.

In the event of an adverse event, the intervention will be discontinued immediately. All participants will have access to comprehensive medical care at University Hospital, including legally required compensation, if applicable.

### Expected outcomes

Photobiomodulation is expected to significantly reduce perineal pain and vulvar edema during the immediate postpartum period, achieving both statistical and clinical significance. Improvements are also expected in sexual function, maternal functioning, patient satisfaction, urinary incontinence, and quality of life.

If confirmed, these findings may support photobiomodulation as an effective, safe, and clinically relevant intervention for postpartum care, with positive effects on postpartum recovery and sexual health.

### Data management

To ensure confidentiality and minimize potential discomfort, participants will be identified using coded abbreviations rather than their names. Interviews and assessments will be conducted in a private setting with restricted access, and participants will have the option of being accompanied during the procedures.

All data will be recorded in standardized Case Report Forms (CRFs) by trained researchers. Data entry will be performed independently by two researchers using a double-entry system to ensure accuracy. Following data entry, the dataset will be checked for inconsistencies and validated before analysis. A coding system will be applied to all variables, and a data dictionary will be developed to standardize data management procedures.

Assessment forms and image records will be stored securely, with access restricted to the principal investigator. Electronic data will be password-protected and stored on secure institutional servers. All research materials will be retained for five years after study completion and subsequently destroyed, including the permanent deletion of digital files.

### Participant retention and follow-up

Strategies to maximize participant retention will include clear communication regarding the importance of follow-up assessments, flexible scheduling of follow-up visits, and reminder contacts by telephone or text message.

Participants who fail to attend follow-up assessments will be documented, and the reasons for withdrawal will be recorded whenever possible. All randomized participants will be included in the analyses according to the intention-to-treat principle.

### Statistical analysis

Statistical analyses will be performed using the Statistical Package for the Social Sciences (SPSS), version 20.0 (IBM Corp., Armonk, NY, USA), adopting a significance level of 5% (*p* < 0.05). Descriptive statistics will be presented as absolute and relative frequencies for categorical variables and as means, standard deviations (SD), and 95% confidence intervals (95% CI) for continuous variables.

The primary analysis of longitudinal outcomes will be performed using linear mixed-effects models. Treatment group (photobiomodulation and sham), time (T0: baseline; T1: immediately after the intervention; T2: 12 h after the intervention; T3: 40 days postpartum; and T4: 3 months postpartum), and the group × time interaction will be included as fixed effects, while participant will be included as a random effect to account for the correlation among repeated measurements within the same participant. The group × time interaction will be considered the primary parameter for determining whether changes in outcomes over time differ between the photobiomodulation and sham groups. Baseline outcome values will be included in the model when appropriate.

Model assumptions will be assessed by examining the distribution of residuals and the homogeneity of variance. If substantial deviations from model assumptions are identified, appropriate data transformations or alternative statistical approaches will be considered.

For baseline comparisons, categorical variables will be analyzed using Pearson’s chi-square test or Fisher’s exact test, as appropriate. Continuous variables will be analyzed using the independent-samples Student’s t-test for approximately normally distributed data or the Mann–Whitney U test for non-normally distributed data.

When a significant group × time interaction is identified, post-hoc pairwise comparisons will be performed to determine differences between groups at each assessment time point and changes within each group over time. The Bonferroni correction will be applied to adjust for multiple comparisons and control the family-wise type I error rate.

The magnitude of the intervention effect will be estimated using mean differences (MD) for continuous outcomes and relative risks (RR) for dichotomous outcomes, with corresponding 95% confidence intervals (95% CI). The number needed to treat for benefit (NNTB) will be calculated for dichotomous outcomes when applicable.

All primary analyses will follow the intention-to-treat principle. For longitudinal outcomes analyzed using linear mixed-effects models, missing outcome data will be handled using all available observations under the assumption that data are missing at random (MAR), without imputing individual missing time points in the primary analysis. The pattern and reasons for missing data will be described and compared between treatment groups. If the proportion of missing data is substantial, a sensitivity analysis using multiple imputation will be performed to assess the robustness of the results under different assumptions regarding missing data.

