### Sample size calculation

The sample size was calculated using G*Power software (version 3.1.9.7), based on a two-tailed independent-samples Student’s *t* test for the comparison of means between two independent groups. A significance level of 5% (α = 0.05), statistical power of 80% (1 − β = 0.80), and an allocation ratio of 1:1 were assumed. Based on the findings of Alvarenga et al. ^16^. a mean perineal pain score of 4.5 (SD = 3.0) was assumed for the experimental group and 2.0 (SD = 2.2) for the sham group, resulting in an estimated effect size (Cohen’s *d*) of 0.784. The analysis indicated a minimum sample size of 54 participants, with 27 participants per group, achieving an actual statistical power of 80.75%. Considering an anticipated dropout rate of 20%, the sample size was increased to 68 participants, with 34 participants allocated to each group [14–16]. 

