### Participant characteristics and outcome assessments

Participants will undergo five assessments: three during the immediate postpartum period (baseline, immediately after the intervention, and 12 h after the intervention), one at 40 days postpartum, and one at 3 months postpartum. The schedule of assessments and assessment instruments is summarized in Table 3.

**Table 3 Tab3:** Detailed description of study outcomes

Outcome	Instrument/test	Description of the instrument/test	Scoring	Assessment timepoint	Clinically meaningful effect
Pain	Numeric Rating Scale (NRS)	A unidimensional instrument widely used to assess self-reported pain intensity.	0 (no pain) to 10 (worst pain imaginable).	T0, T1, and T2	Reduction of ≥ 2 points on the NRS.
	Digital pressure algometer	Assesses the pressure pain threshold in the bilateral peritraumatic region by applying gradually increasing pressure.	Value recorded in kgf/cm².	T0, T1, and T2	Increase in the pressure pain threshold.
Vulvar edema	Standardized photography and measuring tape	Objective assessment of vulvar edema using standardized photographic documentation and measurement of the edematous area.	Measurement in millimeters and photographic analysis.	T0, T1, and T2	Reduction in vulvar edema size.
Immediate postpartum functioning	Likert scale	Assesses difficulty in performing functional activities during the immediate postpartum period (standing up, sitting down, walking, and caring for the newborn).	1 = no difficulty to 5 = extreme difficulty.	T0, T1, and T2	Reduction in functional difficulty.
Patient satisfaction	Visual Analog Scale (VAS)	Assesses participant satisfaction with the treatment received.	0 = no satisfaction to 10 = maximum satisfaction.	T0 and T3	Increased satisfaction compared with the baseline assessment.
Global perceived change	Patient Global Impression of Change (PGIC)	Assesses the participant’s subjective perception of clinical improvement following the intervention.	1 = no change to 7 = very much improved.	T1 and T2	Score ≥ 5, indicating perceived improvement.
Late and remote postpartum functioning	World Health Organization Disability Assessment Schedule 2.0 (WHODAS 2.0)	Assesses functioning across six domains of daily life: cognition, mobility, self-care, getting along with others, life activities, and participation.	1 = no difficulty to 5 = extreme difficulty.	T3 and T4	Reduction in the total WHODAS 2.0 score.

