Vulvar Edema Area the area of vulvar edema will be quantified using digital image analysis with ImageJ software (National Institutes of Health, Bethesda, MD, USA). For each photograph, the edematous region will be manually outlined using either the Freehand Selection or Polygon Selection tool according to the anatomical boundaries of the edema. The software will automatically calculate the area of the region of interest (ROI). Images will be calibrated using a reference scale positioned in the same plane as the photographed area, allowing measurements to be expressed in square millimeters (mm²).

Participant satisfaction with the intervention will be assessed using a Visual Analog Scale (VAS) for satisfaction, ranging from 0 (no satisfaction) to 10 (maximum perceived satisfaction), administered at the final assessment [20]. 

Global perceived change will be assessed using the Global Perceived Effect Scale (GPE), which consists of seven response categories ranging from 1 (no change) to 7 (very much better). This outcome will be assessed immediately after the intervention and again 12 h later [21]. 

Immediate postpartum functioning will be evaluated using a 5-point Likert scale, assessing the level of difficulty in performing activities such as standing up, sitting down, walking, and caring for the newborn.

During the late and remote postpartum follow-up assessments, functioning will be evaluated using the World Health Organization Disability Assessment Schedule 2.0 (WHODAS 2.0), which assesses six domains: cognition, mobility, self-care, getting along with others, life activities, and participation. Responses are scored on a 5-point scale ranging from 1 (no difficulty) to 5 (extreme difficulty) [22]. 

Urinary incontinence will be investigated based on participants’ self-reported symptoms and the International Consultation on Incontinence Questionnaire–Short Form (ICIQ-SF), a validated instrument that evaluates the frequency, severity, and impact of urinary leakage on quality of life. Total scores range from 0 to 21, with higher scores indicating greater symptom severity and impact.

Sexual function will be assessed at 3 months postpartum using the Female Sexual Function Index (FSFI), which comprises 19 items distributed across the domains of desire, arousal, lubrication, orgasm, satisfaction, and pain. Total scores range from 2 to 36, with a cutoff score of ≤ 26.55 indicating possible female sexual dysfunction.

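### For secondary outcomes measured only at two post-treatment visits (WHODAS 2.0, ICIQ-SF, PGIC), the deciding group × time interaction cannot detect a benefit that is equal at both visits

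*Protocol article*

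**What the plan says.** The Statistical analysis section of the protocol article describes one mixed model for longitudinal outcomes. Its fixed effects are group, time with five levels (T0 to T4) and their interaction, with participant as a random effect. It then names the deciding quantity: "The group × time interaction will be considered the primary parameter for determining whether changes in outcomes over time differ between the photobiomodulation" and sham groups. Pairwise comparisons between groups at each visit, Bonferroni-corrected, are planned for when that interaction is significant. A later paragraph promises mean differences or relative risks with 95% confidence intervals. It does not tie them to the interaction, name a visit, or give them a deciding role.

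No outcome in Table 3 is measured at all five time points. The relevant schedule is:

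- NRS pain, pressure pain threshold, vulvar edema and immediate functioning: T0, T1, T2.
- PGIC (called the Global Perceived Effect Scale in the text): T1, T2. Table 1 also marks T0.
- WHODAS 2.0 and ICIQ-SF: T3, T4.
- FSFI: T4.

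For WHODAS 2.0, Table 3 gives the clinically meaningful effect as "Reduction in the total WHODAS 2.0 score". For ICIQ-SF it gives "Reduction of approximately 2.5–5 points; changes of ≥ 4 points represent a clinically important improvement". Neither instrument has a pre-treatment measurement.

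**The concern.** When an outcome has a value before treatment, randomization makes the expected group difference at T0 zero, so a group × time interaction reflects a treatment effect. When every measurement comes after treatment, that reasoning no longer applies. The interaction then compares the group difference at one post-treatment visit with the group difference at another. A benefit already present at the first visit and unchanged at the second contributes nothing to it.

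The rule therefore favors fading or growing effects over stable ones. For WHODAS 2.0 and ICIQ-SF a stable benefit is a plausible form of success, and Expected outcomes anticipates improvement in maternal functioning and urinary incontinence. Because the per-visit comparisons depend on the interaction, the tests that would show a stable benefit are the ones withheld. Apart from adverse events, T3 and T4 in the time factor can serve only the late outcomes, so the rule appears to be meant for them.

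**Working it through.** **1. The plan's own figure.** Sample size calculation uses a design "based on a two-tailed independent-samples Student’s *t* test for the comparison of means between two independent groups", with the settings "A significance level of 5% (α = 0.05), statistical power of 80% (1 − β = 0.80), and an allocation ratio of 1:1 were assumed", "resulting in an estimated effect size (Cohen’s *d*) of 0.784". With n = 27 per group, df = 2n − 2 = 52 and noncentrality = 0.784 × √(27/2) = 2.88. The noncentral t distribution gives power 80.70%, against 80.75% stated. Allowing for dropout, 54/0.8 = 67.5, rounded up to 68. The figures reproduce from d = 0.784. (The means and SDs printed beside it give a different value, 2.5/√((3.0² + 2.2²)/2) = 0.95. That is a separate matter and does not alter the result below.)

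**2. Interaction degrees of freedom under the actual schedule.** These come from the rank of the group + time + group × time design matrix minus the rank without the interaction:

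- T0–T2 outcomes: 6 − 4 = 2
- PGIC (T1, T2): 4 − 3 = 1
- WHODAS 2.0 and ICIQ-SF (T3, T4): 4 − 3 = 1
- FSFI (T4): 2 − 2 = 0

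**3. What the 1-df interaction tests.** With two visits and complete data it is a two-sample t test on each woman's change. Let d₁ and d₂ be the standardized group differences at the two visits and ρ the within-woman correlation.

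- Interaction effect size = (d₂ − d₁)/√(2(1 − ρ)). If d₁ = d₂ this is 0 whatever d, ρ or n may be, so the rejection rate equals α = 5%.
- Averaged group difference, with d₁ = d₂ = d: effect size = d/√((1 + ρ)/2).

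**4. Numbers.** Three inputs are assumptions that the protocol does not give for these outcomes: d = 0.784 (its pain figure, borrowed) or 0.5, ρ from 0.3 to 0.8, and complete data on 27 per group. For example, at ρ = 0.5 the averaged effect size is 0.784/√0.75 = 0.905.

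| ρ | Interaction, equal effect at both visits | Averaged difference, d = 0.784 | Averaged difference, d = 0.5 | Interaction, effect halves from 0.784 to 0.392 |
|---|---|---|---|---|
| 0.3 | 5% | 93.9% | 60.9% | 22% |
| 0.5 | 5% | 90.4% | 54.9% | 29% |
| 0.7 | 5% | 86.6% | 49.8% | 45% |
| 0.8 | 5% | 84.6% | 47.6% | 61% |

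Simulation with 20,000 runs per setting gave interaction rejection rates of 0.047 to 0.054 under an equal effect, over all settings with 27 or 34 per group. With 34 per group the averaged difference has 92–98% power at d = 0.784 and 57–71% at d = 0.5. A halving effect is flagged 27–71% of the time.

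**5. Contrast with outcomes that have T0.** With no difference at T0 and d = 0.784 at T1 and T2, the 2-df interaction has power 69.9%, 84.4% and 97.4% for ρ = 0.3, 0.5 and 0.7 (27 per group). Here the interaction does respond to a treatment effect.

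**The case against.** Several readings stronger than the documents support are tempting.

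- **That a stable benefit would be reported as no effect.** The protocol does not say that a non-significant interaction means no treatment effect. Group is a fixed effect in the same model, and mean differences or relative risks with confidence intervals are promised without the interaction condition. A stable benefit could still appear as an estimate. What stands is that this estimate has no named visit and no deciding role, while the interaction does.
- **That FSFI is untestable.** The rule covers longitudinal outcomes, and FSFI is measured once: "Sexual function will be assessed at 3 months postpartum using the Female Sexual Function Index (FSFI"). It falls outside the rule. Table 3 gives a cutoff, and a mean difference or relative risk can be computed. An article may leave the single-visit test to a fuller document.
- **That the trial's main conclusion is at risk.** The primary aim is perineal pain as change from baseline, measured at T0–T2, where the interaction works. The affected outcomes are secondary, and the Discussion already cautions against reading the 40-day and 3-month results as direct evidence of a long-term effect.
- **That roughly 90% power is being thrown away.** The d of 0.784 was assumed for pain. At d = 0.5 the averaged contrast has only 48–61% power with 27 per group, and the trial was not sized for these outcomes.

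PGIC is the weakest of the three examples. Its schedule differs between Table 1 and Table 3, and its threshold of 5 or more could be handled through the relative-risk route. A change rating made before treatment could not serve as a baseline, however, so a T0 entry would not rescue the interaction. Finally, the five listed time levels may be only the trial's time coding, and a reduction in Table 3 may mean only the favorable direction. Both are wording matters beside the central point.

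**Conclusion.** The concern holds for WHODAS 2.0 and ICIQ-SF, and less cleanly for PGIC. The protocol names a deciding parameter that does not measure treatment benefit on their schedule, and it makes per-visit group comparisons follow from that parameter. This is a stated rule that fits badly, not a detail left to another document.

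The structural result needs no assumed effect size: any benefit equal at both visits gives zero interaction and is flagged at the 5% error rate. The size of the loss does rest on assumptions. With 27 per group, complete data and correlation 0.3–0.8, the averaged group difference would have 85–94% power at d = 0.784, or 48–61% at d = 0.5. An effect that changes between visits can still be flagged. The primary pain outcome is unaffected. The rule should be fixed, but it does not threaten the trial's main inference.

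**What to change.** 1. Limit the interaction-based model to the outcomes measured at T0, T1 and T2, and list only those time levels for it.
2. For WHODAS 2.0, ICIQ-SF and PGIC, make the between-group difference the deciding contrast without requiring a significant interaction. Name one contrast per outcome in advance, such as the average over its two visits, with the two per-visit differences Bonferroni-adjusted. This keeps the added comparisons under control.
3. For clarity, state FSFI as a single between-group comparison at T4.
4. In Table 3, word the WHODAS 2.0 and ICIQ-SF effects as between-group differences, because there is no pre-treatment value from which to reduce.
5. Reconcile Table 1 with Table 3 and the text on PGIC timing (T0 marked or not) and on FSFI (combined T3/T4 column against T4).

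The cost is text only: no added visits, measurements or participants. The change should be made and dated before unblinding, so that the deciding contrast is not chosen after results are seen.
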